# Discontinuation of antidepressant medication in primary care supported by monitoring plus mindfulness-based cognitive therapy versus monitoring alone: design and protocol of a cluster randomized controlled trial

**DOI:** 10.1186/s12875-019-0989-5

**Published:** 2019-07-26

**Keywords:** Antidepressants, Discontinuation, Tapering, Long-term use, General practitioner, Primary health care, Mindfulness-based cognitive therapy

## Abstract

**Background:**

Antidepressant use continues to rise, mainly explained by an increase in the proportion of patients receiving long term treatment. Although treatment guidelines recommend discontinuation after sustained remission, discontinuing antidepressants appears to be challenging for both patients and general practitioners (GPs). Mindfulness-Based Cognitive Therapy (MBCT) is an effective intervention that reduces the risk of relapse in recurrent depression and might facilitate discontinuation by teaching patients to cope with withdrawal symptoms and fear of relapse. The current study aims to investigate the effectiveness of the combination of Supported Protocolized Discontinuation (SPD) and MBCT in comparison with SPD alone in successful discontinuation of long-term use of antidepressants in primary care.

**Methods:**

This study involves a cluster-randomized controlled trial conducted in primary care patients with long-term use antidepressants with baseline and 6, 9 and 12 months follow-up assessments. Patients choosing to discontinue their medication will be offered a combination of SPD and MBCT or SPD alone. Our primary outcome will be full discontinuation of antidepressant medication (= 0 mg) within 6 months after baseline assessment. Secondary outcome measures will be the severity of withdrawal symptoms, symptoms of depression and anxiety, psychological well-being, quality of life and medical and societal costs.

**Discussion:**

In theory, stopping antidepressant medication seems straightforward. In practice however, patients and their GPs appear reluctant to initiate and accomplish this process. Both patients and professionals are in need of appropriate tools and information to better support the process of discontinuing antidepressant medication.

**Trial registration:**

ClinicalTrials.gov PRS ID: NCT03361514 retrospectively registered October 2017.

## Background

Antidepressant use continues to rise. Between 2003 and 2013, antidepressant prescription numbers have doubled in western countries [1], and have been rising with 3% per year in the Netherlands [2]. Despite being effective for some patients in reducing symptoms of depression and anxiety and reducing the risk of depressive relapse [3] antidepressants may also have side effects such as sleep disturbance, weight gain, sexual dysfunction and gastrointestinal bleeding [4, 5]. In addition, they sometimes even go along with more serious adverse events, such as falls, attempted suicide or self harm, stroke and epilepsy [6]. Consequently, current primary care guidelines advise to consider discontinuation of antidepressants 6 months after remission of a depression or 6–12 months after remission of an anxiety disorder. Patients with recurrent depression are advised to discontinue medication after 1–2 years. It is generally recommended to taper slowly, with guidelines suggesting a 50% dose reduction every 2 weeks while monitoring side effects and deploying relapse prevention strategies [7]. The pace of tapering seems important as it appears to influence the risk of relapse in patients with depressive disorder [8].

However, the steady rise of antidepressant use seems to be explained mainly by an increase in long-term users [9]. In the UK and US, 50–65% of patients treated with antidepressants continue to use them for more than 2 years [10–12]. After starting antidepressant medication almost 30% of the patients become chronic users, defined as the consecutive use of any antidepressant for at least 12 months [13]. Despite the general guidelines on tapering antidepressants in primary care, actually discussing and initiating discontinuation appears to be challenging [14, 15]. Stopping antidepressant medication might be hampered by the presence of physical or psychological withdrawal symptoms, including headache, dizziness, electric-shock sensations, sleep disturbance, anxiety and mood swings. These symptoms may easily be misidentified as signs of impending relapse [16]. In addition, earlier unsuccessful attempts to discontinue may provoke further fears for withdrawal symptoms and relapse. Previous research in a sample of 146 inappropriate long-term antidepressant users from 45 general practices in the Netherlands showed that a multidisciplinary, patient tailored advice to discontinue antidepressant medication was rejected in 48% of the cases. The proportion of successful antidepressant discontinuation following this multidisciplinary advice was only 6% [17].

To protect against depressive relapse after the acute phase of depression several psychotherapeutic treatment strategies have evolved [18]. This way alternatives for patients not wanting to maintain antidepressants seem available. Mindfulness Based Cognitive Therapy (MBCT) is one of these approaches of relapse prevention, it is an innovative psychological approach for relapse/recurrence prevention in recurrent depression developed by Segal, Williams & Teasdale [19]. It is an 8-week group-based treatment that integrates elements from mindfulness-based stress reduction (MBSR) [20] and cognitive–behavioural therapy (CBT) [21]. A recent meta-analysis showed that MBCT appears efficacious as a treatment for relapse prevention for those with recurrent depression. MBCT reduces the risk of depressive relapse/recurrence compared with the current mainstay approach, maintenance antidepressants [22]. As MBCT appears to be a viable alternative to antidepressant medication it is possible that mindfulness could provide patients support in the de-identification of thoughts and allowing of uncomfortable physical and mental symptoms, and also help them to deal with possible withdrawal effects.

There is some evidence that MBCT might be useful in supporting tapering of antidepressant medication. Two randomized controlled trials in the UK, offering recurrently depressed patients MBCT with additional tapering support, show successful tapering of Antidepressant Medication (ADM) in 75% [23] and 71% of participants [24]. However, results from a study conducted in the Netherlands were less promising. Only 53% of the patients allocated to the group who received MBCT and tapering support succeeded in tapering their antidepressants [25]. Remarkably, there was a relatively large number of “cross-overs” in this trial, as 12% of patients who were asked to continue their medication after MBCT actually discontinued their antidepressant medication successfully. This latter trial showed that tapering was not necessarily easy even after MBCT, but that the perspective of the patient (e.g. preferences, motives, previous experiences with withdrawal) may have played a significant role. The authors suggested that MBCT for tapering ADM might need to be offered in homogeneous groups of patients who are eager to withdraw from their medication and that it should be specifically tailored to address effects of discontinuation within the mindfulness framework.

Therefore, the aim of this study is to investigate the effectiveness of the combination of supported protocolized discontinuation (SPD) and mindfulness-based cognitive therapy (MBCT) in comparison with SPD alone in successfully discontinuing long-term use of antidepressants in primary care. SPD is carried out by the GP and mental health assistant (MHA). The function of the MHA (POH-GGZ in Dutch this is an abbreviation for Practice Support Professional for Mental Health Care) was installed in the Netherlands in 2008 to support GPs in diagnosing, treating and referring patients with mental health problems. In 2016 in the Netherlands 81% of all GP’s have arranged a MHA in their practice.

Our main hypothesis is that long-term users of antidepressants in primary care receiving SPD + MBCT will more often successfully discontinue their medication within a period of 6 months than patients receiving SPD alone. Our secondary hypotheses are that, in comparison with patients receiving SPD alone, patients who receive SPD + MBCT will have a lower rate of relapse/recurrence of a depressive or anxiety disorder, a lower rate of restarting medication, suffer less from withdrawal symptoms, report less depression, anxiety, and ruminative brooding, and more mindfulness skills, self-compassion and psychological wellbeing over the 12 months follow-up period.

## Methods

### Design

This study is designed as a cluster-randomized controlled trial conducted in primary care with GP’s that work with a MHA, randomizing patients at the level of their GPs over a) Supported Protocolized Discontinuation (SPD) alone or b) SPD with additional Mindfulness-Based Cognitive Therapy (MBCT). We choose cluster randomisation for practical reasons, i.e. to simplify the procedures within the GP Practices. The patient, GP and the research team will be aware of the allocated condition. However, the mental health assistant MHA of the GP will be blind to the condition as much as possible by asking the GP not to inform the MHA about their allocated study arm. In addition we will ask participants in the SPD + MBCT condition to refrain from informing pro-actively about their participation in the MBCT. Regarding recruitment a detailed explanation is written in the Procedure. For a study flowchart see Fig. 1. The study protocol has been approved by the Medical Ethics Committee Arnhem-Nijmegen and registered under number 2016–2527.

**Fig. 1 Fig1:**
[figure not shown]
Flow chart of the recruitment and study procedure

### Participants

Patients will be recruited from GPs with a mental health assistant in the north, middle and east part of the Netherlands and only included in the study after informed consent has been obtained.

#### Inclusion criteria

In order to be eligible to participate in this study patients must have received prescriptions for antidepressants in primary care for at least the past 9 months and be 18 years or older.

#### Exclusion criteria

Patients who meet any of the following criteria will be excluded from the study: current treatment by a psychiatrist; current substance use disorder; non-psychiatric indication for long-term antidepressant usage (i.e. neuropathic pain); having participated in a mindfulness training (> 3 sessions) within the last 5 years; or inability to perform the assessments due to cognitive or language difficulties.

#### Safety and monitoring

Patients will be free to increase the dosage or restart their medication at any time during the study. In case of difficulties during the discontinuation process patients are advised to contact their GP and or MHA. Suspected serious adverse events will be recorded and reported to the Medical Ethics Committee Arnhem-Nijmegen.

### Sample size

Based upon earlier research we expect a discontinuation rate for patients in the SPD condition of 15% and a 40% discontinuation rate for patients in the SPD + MBCT condition. We used data from Eveleigh [17] to predict discontinuation in the SPD condition (where 6% successful discontinuation was observed according to very strict criteria, and we made adaptations to align with the context of the current setting, e.g. all patients had a clear intention to taper). To estimate the rate in the SPD + MBCT condition, we looked at studies with available data on adherence to tapering after MBCT, ranging between 53 and 71% [23–25]. Again we made a conservative adaptation of 40% to account for differences in time frame (6 versus 15 months), intention-to-treat versus per-protocol sample, and considering the difficulties in discontinuation and withdrawal symptoms as mentioned in the literature [16]. The following assumptions were used in the sample size calculation: power 80%, alpha of 5% and two tailed testing. Due to the fact that the trial will be cluster randomized, the calculated number of patients assuming individual randomization, has to be inflated by a design factor. To account for this an intra-class correlation (ICC) of 0.05 was used, which is commonly used for research including outcome measures [26]. With regard to the mentioned research we also assume a dropout rate of 15%. Taking these figures into account a total of 24 GPs have to be included, with 138 patients participating in the study; including 69 patients per described condition; presenting an estimate of 5 participating patients per GP.

### Procedure

Eligible GPs will be informed about the study and requested to participate. GP’s will be randomly allocated to either SPD alone or SPD + MBCT. The GPs are asked to identify patients using antidepressant medication for more than 9 months in their electronic prescription system. Between 2016 and 2018 interested GP’s will invite their long-term-users of ADM to discuss tapering via a letter and return form. GPs are requested to inform the research team about the number of patients who will not get an invitation including the reason(s).Patients’ reply forms will be collected by the research team and interested patients will be invited to complete the online screening questionnaire which includes demographic characteristics, ADM-use, the Patient Health Questionnaire [27] and Generalized Anxiety Disorder [28]. Subsequently, they will receive an information brochure about tapering, a decision aid and an invitation to make an appointment with their GP. Patient and GP are encouraged to use the decision aid as a conversation guideline to make a shared decision on whether or not to discontinue the antidepressant medication. After having consulted their GP about tapering and if they decide to start tapering, patients will receive an invitation to participate in the RCT and an invitation for a research interview. During the interview written informed consent that has been approved by the Medical Ethics Committee of Arnhem-Nijmegen will be obtained. The psychiatric structured diagnostic interview that will be conducted [29] will take about 60–90 min altogether. Patients will also be requested to complete baseline measures online. Thereafter patients will be advised to plan meetings with the Mental Health Assistant for their SPD. Those patients allocated to SPD + MBCT will be invited to participate in the first upcoming MBCT course. Follow up measurements take place six, nine and 12 months after baseline using telephone interviews and online questionnaires. The first assessment took place in February 2017, the last assessment will take place in July 2019.

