### Randomization and statistical analysis

To prevent a crossover effect between the interventions, cluster-randomization will be performed with the GP as the unit of clustering. A senior academic statistician will produce the randomization schedule based on a stratified block randomization. Stratification variables consist of region (north, central and east Netherlands) and type of practice (single versus group practice). This schedule will be send in a protected Excel-sheet to a research assistant who will allocate the GP in order of their entry to either intervention or control group. The research assistant will communicate the allocation to the researcher who will, in turn, communicate this to the GP. We are not able to keep the SCID interviewer blind to the patient’s condition. The clinical outcome data will be analysed and reported according to the CONSORT guidelines, i.e. both on an intention-to-treat and per protocol basis. With regard to missing data, sensitivity analyses will be conducted with different types of imputation. Multilevel analyses will be used to account for the hierarchical structure of the data (i.e. multiple assessments nested within patients, patients nested within GPs, and GPs nested within practices).

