### Secondary analyses

We will use Cox regression analysis for differences in time to relapse/recurrence in depression and/or anxiety and multilevel regression analysis for all other secondary outcomes. Baseline scores of all continuous variables will be included as covariates in the respective analyses.

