## Discussion

Both patients and professionals seem to call for appropriate tools and information to better support the process of discontinuing antidepressant medication. In the current study we will address this gap by devising a protocol for shared decision making and the accompanying materials (i.e. information brochure, decision aid, and tapering protocol). This may serve a structured and comprehensive way to approach discontinuation.

One of the strengths of this study is its inclusive sampling strategy, allowing all patients with long-term ADM use to consider tapering and participation. Rather than a priori precluding patients with a certain level of symptomatology, for example with depressive or anxiety disorder, we used a shared decision making approach (including topics related to psychological functioning and effectiveness of antidepressant medication) to define the final RCT population. The decision to taper an antidepressant seems multifaceted, and probably does not solely depend on the level of symptoms. Another advantage of this strategy is that rather than tapering, patients and their GPs might consider switching to a different medication if that seems more appropriate.

In addition this will be the first study that will directly compare MBCT to facilitate discontinuation as an add-on to support in general practice, with support alone. This study will provide more information about the entire process of discontinuation of antidepressants in a population of long-term users in general practices, including the views and preferences of GPs and patients with regard to discontinuation, the value of using psycho-education material about tapering, and the possible value of MBCT to support the process.

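### As written, GPs know their arm before they select, invite and counsel patients, so the arms may differ at entry, and the article names no baseline or stratification covariate for the primary model

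*Protocol article*

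**What the plan says.** All references are to the protocol article.

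- **Allocation, then identification.** Under Procedure, GPs "will be randomly allocated to either SPD alone or SPD + MBCT. The GPs are asked to identify patients using antidepressant medication". Under Randomization and statistical analysis, GPs are allocated in order of entry, and "The research assistant will communicate the allocation to the researcher who will, in turn, communicate this to the GP".
- **Who knows.** Under Design: "The patient, GP and the research team will be aware of the allocated condition". Only the mental health assistant is kept blind, as far as possible.
- **GP's role in entry.** Under Procedure, GPs search their prescription system and send the letters. They report how many patients they did not invite, and why. Later, "Patient and GP are encouraged to use the decision aid as a conversation guideline to make a shared decision".
- **Trial invitation.** Also under Procedure: "After having consulted their GP about tapering and if they decide to start tapering, patients will receive an invitation to participate in the RCT". Consent and baseline measures come next, and the invitation to the MBCT course is listed after them.
- **Population.** The Discussion says that shared decision making, rather than a symptom threshold, is used "to define the final RCT population".
- **Primary model.** Primary analysis gives a repeated-measures multilevel logistic model comparing the two conditions and names no covariate. Under Secondary analyses: "Baseline scores of all continuous variables will be included as covariates in the respective analyses". Region and practice type stratify the randomisation but are not named in the primary model.

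**The concern.** Cluster randomisation makes the GPs comparable in expectation. Their enrolled patients are comparable only if enrolment does not depend on the arm. Here, someone who knows the arm helps decide who is invited and takes part in the conversation that settles who tapers. A GP with a mindfulness course to offer may encourage hesitant patients. A GP without one may end up enrolling only the most determined. The opposite pattern is also conceivable.

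The article itself treats the selected trait as prognostic and the filter as wide:

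- Sample size raises the expected SPD rate from an observed 6% to 15%, giving patients' intention to taper as an example of the reasons.
- Background reports that advice to discontinue was rejected in 48% of cases in an earlier Dutch study. It also suggests that patients' preferences and motives may have mattered in an earlier tapering trial.

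At stake is the primary comparison. A difference present at entry would be read as a treatment effect, or would hide one, and a larger sample would not remove it.

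**Working it through.** **1. Order of the steps, as the article gives them**

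| Step | Who acts | Same step in both arms? |
|---|---|---|
| GP allocated and told the arm | research team | – |
| Prescription search, letters, some patients left out | GP | yes |
| Reply form, online screening (PHQ, GAD, ADM use) | patient, research team | yes |
| Brochure, decision aid, talk on whether to taper | GP and patient | yes |
| Trial invitation, interview, consent, baseline | research team, patient | yes |
| Invitation to the MBCT course | research team | **no** |

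Allocation is first needed at the last row. As described, the GP has it from the first.

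**2. The plan's own figures reproduce and are not in dispute**

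Inputs (Sample size): 15% versus 40%, two-sided 5%, power 80%, ICC 0.05, 5 patients per GP, dropout 15%.

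- Individual randomisation, pooled formula: n = [1.960·√(2·0.275·0.725) + 0.842·√(0.15·0.85 + 0.40·0.60)]² / 0.25² = 48.9, so 49 per arm.
- Design effect: 1 + (5 − 1)·0.05 = 1.20, so 49·1.20 = 58.8.
- Dropout: 58.8/0.85 = 69.2 per arm, 138.4 in total, against the stated 69 and 138.

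These figures assume that the only difference between arms is the treatment.

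**3. Size of a spurious difference when treatment does nothing (assumed inputs, not in the article)**

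Bias = (difference between arms in the share of motivated patients) × (difference in stopping rate between motivated and other patients).

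- 20-point imbalance, 20-point gap: 0.20·0.20 = 4 points.
- 20-point imbalance, 40-point gap: 0.20·0.40 = 8 points.
- 10-point imbalance, same gaps: 2 and 4 points.

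**4. Effect on the false-positive rate (also assumed inputs)**

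Let ready patients stop at 30% and others at 5%. With 40% ready in the SPD arm, its rate is 0.40·0.30 + 0.60·0.05 = 15%, the planned value. The effective n per arm is 69/1.20 = 57.5. With d the spurious difference and SE = √[(p₀(1−p₀) + p₁(1−p₁))/57.5], the chance of a significant result is 1 − Φ(1.96 − d/SE) + Φ(−1.96 − d/SE).

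| Ready share, MBCT arm | Rate | d (points) | Chance of p < 0.05 |
|---|---|---|---|
| 40% | 15.0% | 0 | 5.0% |
| 50% | 17.5% | +2.5 | 6.5% |
| 60% | 20.0% | +5.0 | 10.9% |
| 70% | 22.5% | +7.5 | 17.9% |
| 30% | 12.5% | −2.5 | 6.8% |
| 20% | 10.0% | −5.0 | 12.8% |

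**5. Does the described analysis offset this?**

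The primary model includes the baseline assessment as a repeated measure. Every patient is a user at baseline, so that value cannot separate the arms or adjust for anything. The baseline-covariate sentence stands under Secondary analyses and concerns continuous scores. The primary outcome is binary.

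**The case against.** Several points on the other side have weight.

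- **Patient knowledge.** A reader might infer that patients know their arm before consenting. The Design section says they will be aware but gives no time, and Procedure lists the course invitation after baseline. The inference is not supported. The concern does not need it, because the GP's knowledge is enough.
- **Timing for the GP.** The article says how the GP is told, not on what date, and the flow chart is not shown. The reading rests on the order of the sentences in Procedure and on the absence of any described delay or masking.
- **Advice by arm.** A reader might infer that GPs advise patients to taper. The text describes a shared decision on whether to do so, with the same decision aid in both arms.
- **Adjustment.** A reader might conclude that the primary analysis is unadjusted. The article only names no covariate. The model accounts for clustering, and a full protocol or SAP not shown may list covariates. The absence is context for the fix, not a fault by itself.
- **Safeguards.** The prescription search, the log of uninvited patients with reasons, reply forms handled by the research team, screening before the GP talk and the promise of CONSORT reporting all reduce the risk or make it visible. None takes the unblinded GP out of selection and counselling.
- **Too late.** GP invitations ran from 2016 to 2018, and the last assessment was due in the month of publication. This limits what can still be changed, but not whether the bias is possible.

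**Conclusion.** The point holds as a design weakness in the primary comparison. As Procedure and Randomization and statistical analysis are written, GPs are allocated and told their arm before they identify, invite and counsel patients, and the shared decision on tapering fixes the trial population. The arms may therefore differ at entry, in either direction, and cluster randomisation gives no protection.

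The documents do not show that such a difference arose, nor how large it would be. The 4 to 8 points are an illustration on assumed inputs. They are at most about a third of the planned 25 points (8/25 = 0.32), and smaller imbalances give proportionally less. On the second set of assumptions, the false-positive rate rises from 5% to between 6.5% and 17.9%, depending on the size and direction of the imbalance.

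**What to change.** **For any GP not yet told the arm.** Release the allocation only after that GP's invitation list is locked and, for each patient, only after consent and baseline, when the MBCT invitation goes out. The existing steps stay as they are. The cost is that GPs and patients learn the arm later, and that the information letter must describe both arms, which needs an ethics amendment. One gap remains: once a GP's first patient is invited to the course, the GP may infer the arm for patients still deciding. Recruiting each GP's patients close together narrows it.

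**For GPs already informed.** On the article's dates this is probably all of them.

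- Adjust the primary model for region, practice type, screening PHQ and GAD scores, baseline IDS-C and baseline ADM use, specified before outcomes are compared by arm. This costs only SAP wording. At the planned rates about 69·0.15 + 69·0.40 = 38 patients would stop, so the list should stay this short and scores should enter as single linear terms.
- Report by arm the numbers listed, invited, replied, deciding to taper and consented. The log of uninvited patients and the reply forms already supply part of this.
- State as a limitation that adjustment cannot remove selection on unmeasured motivation, since none of these covariates measures it.
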